## Abstract

**Background::**

Cancer-related fatigue (CRF) is a major symptom experienced by lung cancer patients receiving chemotherapy and radiation therapy. Since CRF has a multidimensional influence on cancer patients, they may experience physical weakening, a decline in cognitive function, and depression from emotional consequences. Kyung-Ok-Ko is used for improving fatigue or weak physical constitution. It is known to be effective in immune activation, reducing fatigue, and enhancing cognitive function. Although Kyung-Ok-Ko is clinically used for the treatment of CRF, its efficacy and safety against CRF in lung cancer patients are yet to be studied. Therefore, we aimed to investigate the efficacy and safety of Kyung-Ok-Ko.

**Methods::**

This is a randomized, placebo-controlled, patients-assessor blind, parallel-group, single-center clinical trial. Lung cancer patients with CRF, after termination of chemo or radiation therapies, are randomized in a 1:1 ratio to receive either Kyung-Ok-Ko or placebo for 6 weeks. The primary outcome is Brief Fatigue Inventory (BFI). The secondary outcomes include Visual Analog Fatigue Scale (VAFS), Functional Assessment of Cancer Therapy (FACIT) Fatigue scale, Hospital Anxiety Depression Scale (HADS), Montreal Cognitive Assessment Korean version (MoCA-K), and Korean pattern identification questionnaire. Adverse events are evaluated by Common Terminology Criteria for Adverse Events (CTCAE). All outcomes and adverse events are assessed at the baseline, mid-treatment, post-treatment, and at 1-month follow-up.

**Discussion::**

This study investigates whether Kyung-Ok-Ko can alleviate CRF in lung cancer patients. The results of this study will provide clinical evidence for the application of Kyung-Ok-Ko in the treatment of CRF in lung cancer patients.

**Trial registration::**

Korean Clinical Trial Registry (http://cris.nih.go.kr; registration number: KCT000666).

Trial status: Currently, participant recruitment is ongoing.

## Introduction

1

Lung cancer is the leading cause of deaths due to cancer in both men and women worldwide.^[1]^ In the United States, 0.25 million new cases of lung cancer along with the highest mortality rate was reported in 2018.^[2]^ Lung cancer treatments involve multimodality approaches, including surgery, radiotherapy, and cytotoxic chemotherapy, or molecularly targeted agents. During or post-treatment, a number of cluster symptoms, such as anxiety, fatigue, and dyspnea, appear.^[3]^ About 60% to 96% of patients who receive anticancer treatments complain of fatigue.^[4]^

Cancer-related fatigue (CRF) has been referred to by a panel of the National Comprehensive Cancer Network (NCCN) as a distressing, persistent, subjective sense of physical, emotional, and/or cognitive tiredness or exhaustion related to cancer or cancer treatment that is not proportional to recent activity and interferes with usual functioning.^[5]^ Since the influence of CRF on cancer patients is multidimensional, they may experience physical weakening, a decline in cognitive function due to deteriorating mental strength, and depression from emotional consequences.^[6]^

CRF is experienced more by lung cancer patients compared to other types of cancer, and many patients were reported to experience CRF with disabilities.^[7]^ It decreases the patient's quality of life, resulting in reduced compliance with chemotherapy, and ultimately has a negative effect on the survival of the patient; it is an index for the decreasing survival rate of cancer patients.^[8,9]^ An 8-year long cohort study, comprising 2405 lung cancer patients, was conducted and among the symptoms of fatigue, coughing, and dyspnea that the patients frequently complained of, only fatigue was identified as a significant predictor of the poor 4-year and 5-year survival rate.^[10]^ In addition, according to a recently reported study, not only improving the quality of life but also self-evaluation of the symptoms affecting the quality of life alone was shown to increase the survival rate in patients receiving cancer treatment.^[11]^

The major reasons for CRF are the side effects of cancer treatment. Although the exact mechanism is not known, all treatments, including chemo and radiation therapy, molecular targeted agents, and surgical treatment can induce CRF.^[5]^ Although CRF is induced by various factors, many studies have reported inflammation as the common factor of the mechanism.

Since CRF is the main reason for the interruption in treatment or exacerbation of the disease, much effort has been focused on the management of CRF. However, it remains underdiagnosed and undertreated, without any standard therapy until now.

Kyung-Ok-Ko is a prescription, which is described in Donguibogam, a traditional Korean medicine book, and consists of Ginseng Radix, Poria Sclerotium, Rehmanniae Radix Crudus, and honey. It has been widely used for improving fatigue or weak condition. It has been developed as a traditional Korean medicine based on national standards approved by the MFDS (Ministry of Food and Drug Safety). It is reported via in *vitro* and clinical studies that Kyung-Ok-Ko activates the immune system,^[12]^ reduces fatigue,^[13,14]^ and enhances the cognitive function.^[15]^ Anti-inflammatory effects have also been reported, as a supporting mechanism.^[16–18]^

Although Kyung-Ok-Ko is used for alleviating fatigue, research on CRF in lung cancer patients is limited. Therefore, we aimed to identify the efficacy and safety of Kyung-Ok-Ko on lung cancer patients experiencing CRF.

## Methods

2

### Objective and design

2.1

This is a randomized, placebo-controlled, patients-assessor blind, parallel-group and single-center clinical trial. This study was designed to evaluate the efficacy and safety of Kyung-Ok-Ko in lung cancer patients who have received cancer treatment and are experiencing CRF. The trial will be conducted for a total of 10 weeks, as patients who experienced CRF 2 weeks after completing cancer treatment will take the clinical trial drug for 6 weeks, followed by a 4-week observation period. A flow diagram of the study is presented in Figure 1.

**Figure 1 F1:**
[figure not shown]
Study flowchart.

### Randomization, allocation, and blinding

2.2

Subjects are randomized in a 1:1 ratio to the experimental group (Kyung-Ok-Ko group) and control group (placebo group). For randomization, a statistician independent of this clinical trial will use SAS ver.9.1.3 (SAS Institute Inc., Cary, NC) for Microsoft Windows to randomly assign numbers to create a randomization table. The experimental group or placebo group assignments according to the table of random numbers and random numbers generated using SAS are kept by a third party until termination or completion of the trial, and investigators do not require them. The study drug and placebo are assigned and managed by a code and a patients-assessor blind method, where the investigators and subjects cannot distinguish study drug and placebo, was followed. For this purpose, the placebo was manufactured similar to the study drug in terms of appearance, flavor, and scent. The manufacturing company conducted code labeling assigned for the study drug and placebo, and a third party matches the random number and code. When registering each study subject, the third party provided the management number of the study drug or placebo that has been matched with the random number to the investigator via telephone, text message, or mobile communication application. Clinical trial drug and placebo were kept in the pharmacy of Kyung Hee University Korean Medicine Hospital Clinical Trial Center (K-CTC) and was delivered to the subjects by a pharmacist who was kept blind. If the blinding should be broken prior to completion of the clinical trial due to serious adverse events (SAEs) during the clinical trial period, the reasons for breaking blindness will be reviewed and approved before breaking the blindness by the principal investigator.

### Patients

2.3

#### Inclusion criteria

2.3.1

(1)Men and women aged above 19 years.(2)Lung cancer patients who received cancer treatment (chemo and radiation therapy).(3)Patients who have completed cancer treatment >2 weeks ago and do not have any further cancer treatment plans.(4)Patients experiencing fatigue, with brief fatigue inventory (BFI) ≥4.(5)Patients with Eastern Cooperative Oncology Group (ECOG) scale ≤2.(6)Patients who voluntarily decided to participate in this clinical trial and signed the consent form.

#### Exclusion criteria

2.3.2

(1)Patients suspected of relapse or progression according to chest CT or chest X-ray.(2)Patients with hemoglobin level <9 g/dL, or platelets <50 000/mL, or absolute neutrophil count <1000/mL.(3)Patients with uncontrolled thyroid disorder (free thyroxine >1.79 ng/dL, thyroid stimulating hormone >10 μm/dL).(4)Patients with moderate liver and kidney impairment (increase in aspartate transaminase (AST), alanine transaminase (ALT) by >3 times, or increase in creatinine by >2 times).(5)Patients who do not expect >6 months of life expectancy after cancer diagnosis.(6)Patients diagnosed and treated for severe dementia (Montreal Cognitive Assessment Korean version, MoCA-K <10), severe depression (Hospital Anxiety Depression Scale, HADS >15).(7)Patients who are deemed difficult for clinical trial performance.(8)Early-stage lung cancer patients who are treated with surgery alone and late-stage lung cancer patients who are not receiving cancer treatment.(9)Patients who received oriental medicine or pharmacotherapy (methylphenidate, modafinil, bupropion) for the purpose of improving CRF in the last 4 weeks.(10)Patients who are pregnant or breastfeeding.(11)Patients who did not agree to contraception during the clinical trial period.(12)Patients who participated in a clinical trial for the same disease, in the last 3 months.(13)Patients who are not eligible to participate in this trial at the discretion of the investigator.

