##### Hospital Anxiety Depression Scale (HADS)

2.5.2.3

The HADS is an efficient screening tool generally used to assess the anxiety and depression of hospitalized cancer patients.^[21]^ It is composed of 2 subcategories, anxiety and depression, with a total of 14 questions, consisting of 7 questions for anxiety and 7 questions for depression. Each question is based on a 3-point scale, with a total of 21 points possible for each subcategory of anxiety and depression. A higher score indicates a high degree of anxiety and depression, where 0 to 7 points indicate no anxiety and depression, 8 to 10 points suspect anxiety and depression, and >11 points indicate anxiety and depression.^[21]^ Moreover, the total scores refer to a combination of anxiety and depression scores and classified as mild, ranging from 8 to 10, moderate from 11 to 14, and severe from 15 to 21 points.^[22]^ Measurements are taken at the baseline, 2 weeks, 4 weeks, 6 weeks, and 10 weeks after treatment.

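### The exclusion limits for platelets, neutrophils and TSH carry unworkable units, and the HADS limit names no score and does not match the article's own severity bands

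*Protocol article*

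**What the plan says.** **Blood counts and TSH.** In section 2.3.2 of the protocol article, criterion 2 excludes patients with platelets below 50 000 per mL or "absolute neutrophil count <1000/mL". Criterion 3 defines uncontrolled thyroid disorder partly by "thyroid stimulating hormone >10 μm/dL".

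**HADS in the exclusion criteria.** Criterion 6 covers patients diagnosed with and treated for severe dementia, defined by a MoCA-K limit, and "severe depression (Hospital Anxiety Depression Scale, HADS >15". It names neither a subscale nor the total.

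**HADS as an outcome.** Section 2.5.2.3 describes seven anxiety and seven depression questions, "with a total of 21 points possible for each subcategory of anxiety and depression". It bands these scores at 0 to 7, 8 to 10 and above 11. It then says that "the total scores refer to a combination of anxiety and depression scores and classified as mild, ranging from 8 to 10", with moderate at 11 to 14 and "severe from 15 to 21 points".

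**The concern.** These numbers decide who enters the trial. A count limit in the wrong unit does no screening when applied as written, in patients who have recently finished chemotherapy or radiotherapy. A TSH limit with no valid unit cannot be applied without guessing. A HADS limit that could refer to a score running to 21 or to one running to 42 selects different patients depending on the reading. HADS is also a secondary outcome, so the choice affects the range of its baseline values.

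The abstract says recruitment is ongoing, so a correction can still help.

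**Working it through.** **Blood counts.** Inputs: the two limits in criterion 2, and 1 mL = 1000 microlitres.
- Platelets: 50 000 / 1000 = 50 per microlitre.
- Neutrophils: 1000 / 1000 = 1 per microlitre.

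Read literally, practically no patient falls below either value. If per microlitre was meant, the printed limits are too low by a factor of 1000. The article does not state the intended denominator, so that factor is conditional.

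**TSH.** As printed, the unit is micrometres per decilitre, a length over a volume. Haemoglobin (g/dL) and free thyroxine (ng/dL) in the neighbouring limits have proper concentration units, so the fault is specific to this entry.

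**HADS range.** The article's own subscale maximum reproduces: 7 questions × 3 points = 21. The combined maximum is 2 × 21 = 42, so the total can take 43 values (0 to 42). The bands attached to the combined score stop at 21. The values above the top band are 22 to 42, or 42 − 22 + 1 = 21 of 43.

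**HADS cut against the bands.**

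| Item | Section 2.3.2 | Section 2.5.2.3 |
|---|---|---|
| Score used | Not named | Severity bands placed on the combined score |
| Severe from | Above 15, so 16 upward | 15 |
| Upper end | 21 if a subscale, 42 if the total | 21 |

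A score of exactly 15 is severe in section 2.5.2.3 but not excluded in section 2.3.2. For MoCA-K, the limit in the same criterion (below 10) agrees exactly with the severe band in section 2.5.2.4, so the HADS mismatch departs from the article's own pattern.

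**Effect on the design.** The sample size uses BFI means of 3.4 and 5.2, SDs of 1.6 and 1.9, a 0.05 significance level, 90% power and 10% dropout. Averaging the variances gives SD = √((1.6² + 1.9²)/2) = 1.756. With a difference of 5.2 − 3.4 = 1.8 and a two-sided test (assumed), the exact t calculation needs 22 per arm (power 0.913). Then 22 / 0.9 = 24.4, rounded up to 25 per arm, or 50 in all, as the article states. None of the limits above enters this calculation.

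**The case against.** The strongest reply is that this is a journal article and the approved protocol is not shown. The units may be a copying or typesetting slip, and site staff may have used the units their laboratory reports. That stands as far as consequences go: the article cannot show that anyone was wrongly admitted or refused. It does not remove the error from the public text. Loss of a micro sign in text conversion is also an unlikely explanation, because that character survives in the TSH limit in the next criterion.

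A reader might infer that these limits screen out the wrong patients. For the counts that does not follow, since limits this low fail to screen anyone out. The TSH limit is unusable, not misdirected. Nor does it follow that patients have no safety protection: criterion 13 lets the investigator exclude at discretion, so the gap lies in the count rule, not in the whole screen.

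A reader might also infer that a patient with anxiety 8 and depression 8, total 16, would be excluded as severely depressed although each score is only in the suspected band. That requires the total-score reading and requires the cut to act alone. Criterion 6 also speaks of diagnosis and treatment, so the score may only qualify an existing diagnosis. This exclusion is not established.

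Similarly, the mismatch at 15 should not be claimed for the subscales as the article stands, because it gives them no severe band.

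Finally, section 2.11 compares mean change in HADS, so no severity band enters a test, and eligibility is settled before allocation, so any ambiguity acts on both arms alike. That stands, and it limits the point to who enters the trial and how clearly the rule is stated.

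**Conclusion.** The point holds as a defect in the printed eligibility limits:
- The platelet and neutrophil limits equal 50 and 1 per microlitre and would exclude practically nobody if applied literally. The 1000-fold figure assumes that per microlitre was intended.
- The TSH limit cannot be applied as printed.
- The HADS limit names no score. Section 2.5.2.3 contradicts itself by placing bands that end at 21 on a score that reaches 42, leaving 21 of 43 values above the top band. Its severe band includes 15, which the exclusion does not.

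The documents do not show that any patient was wrongly screened. Sample size, alpha, power and the primary BFI comparison do not change. Because these are decision limits in a trial still recruiting, they should be corrected.

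**What to change.** 1. Correct the units of the platelet, neutrophil and TSH limits against the approved protocol and the units the trial laboratory reports.
2. State which HADS score the exclusion uses, and whether the score excludes by itself or only together with an existing diagnosis and treatment.
3. Reconcile the HADS cut in section 2.3.2 with the bands in section 2.5.2.3, and state which score those bands belong to. The clinical lead should confirm all intended values. This review does not propose any.
4. Check the screening log for the limits actually applied. If they were the intended ones, only the published text needs correcting.

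The cost is a short correction or amendment and a log check, with no new tests and no change to the analysis.

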#### Withdrawal criteria

2.3.3

(1)Subjects who received treatment that could affect the outcome without the investigator's instructions during the study period.(2)Subjects who do not follow clinical study protocol or have compliance <80%.(3)Subjects who cannot continue clinical trial due to adverse events (AEs) or if serious AEs occurred.(4)Subjects who withdraw consent.(5)Subjects who use methylphenidate, modafinil, bupropion, and oriental medicines during clinical trial, which can influence fatigue improvement.(6)Subjects who are determined by the investigator to be ineligible for participation in the clinical trial.

### Interventions

2.4

#### Experimental group

2.4.1

The experimental group is administered Kyung-Ok-Ko, which is a dark-brown paste preparation (23.5 g per package), twice a day for a total of 6 weeks. Kyung-Ok-Ko is manufactured by Kwang Dong Pharmaceutical Co., Ltd (Seoul, Korea), which is approved by the MFDS in accordance with the Korean Good Clinical Practice (GCP) regulations. The 23.5 g Kyung-Ok-Ko is composed of 7.98 g of Rehmanniae Radix Crudus, 2.48 g of Poria Sclerotium, 1.24 g of Ginseng Radix, and 8.3 g of honey and other excipients. The subjects receive a 14-day package per visit.

#### Placebo group

2.4.2

The placebo group is administered placebo Kyung-Ok-Ko (23.5 g per package) twice a day for a total of 6 weeks. The placebo is manufactured by Kwang Dong Pharmaceutical Co., Ltd, similar to the physical traits of the clinical trial drug. The placebo that is very similar in size, flavor, scent, and color without the key ingredients is used. The placebo is composed of glucose, sucrose, lactose, corn starch, D-sorbitol, xanthan gum, and caramel color. With a 2-week follow-up, the subjects received a 14-day package per visit.

#### Management of the drug

2.4.3

The clinical trial drug is kept in airtight containers at room temperature (21–30°C). The clinical trial drug is administered by the pharmacist in accordance with the investigator's prescription, and the pharmacist accurately records the clinical trial drug provided to the study subjects and management status. Since this is a double-blind clinical trial, study subjects are only identifiable through their identification number, and information about the prescribed and collected clinical trial drug should be appropriately recorded. Upon termination or completion of the clinical trial, the pharmacist must return the unused clinical trial drug to the sponsor, retain the proof of return, and the sponsor shall dispose of the returned clinical trial drug.

### Outcomes

2.5

#### Primary outcome

2.5.1

##### Brief Fatigue Inventory (BFI)

2.5.1.1

The BFI is a tool developed for the fast and simple measurement of fatigue and is widely used in studies.^[19]^ It is composed of 9 questions, with 3 questions for the degree of CRF and 6 questions for the effects of CRF. Each question is scored from 0 to 10 points, where a higher score indicates severe symptoms; 1 to 3 point is mild, 4 to 6 point is moderate, and 7 to 10 point is severe. Measurements are taken at the baseline, 2 weeks, 4 weeks, 6 weeks, and 10 weeks after treatment (Table 1).

**Table 1 T1:**
[figure not shown]
Trial schedule.

#### Secondary outcomes

2.5.2

##### Visual Analogue Fatigue Scale (VAFS)

2.5.2.1

The VAFS measures from 0 (not tired at all) to 10 (very tired) and classified as: Grade 1 or mild (1,2,3), Grade 2 or moderate (4,5,6), and Grade 3 or severe (7,8,9,10) using National Cancer Institute Common Toxicity Criteria version 4.03. Measurements are taken at the baseline, 2 weeks, 4 weeks, 6 weeks, and 10 weeks after treatment.

##### Functional Assessment of Cancer Therapy (FACIT) Fatigue scale

2.5.2.2

The FACIT Fatigue scale is composed of 13 questions, and the cancer patient is required to give a score to the statement that best represents his or her weekly experience.^[20]^ The 13 questions of this measurement tool are based on the cancer patient's feelings and experience with fatigue, eating and sleeping with fatigue, activity status, and fatigue experienced in the past week. It is scored from 0 points for ‘Strongly disagree’ to 4 points for ‘Strongly agree’, where a higher score indicates a high degree of fatigue. Measurements are taken at the baseline, 2 weeks, 4 weeks, 6 weeks, and 10 weeks after treatment.

##### Hospital Anxiety Depression Scale (HADS)

2.5.2.3

The HADS is an efficient screening tool generally used to assess the anxiety and depression of hospitalized cancer patients.^[21]^ It is composed of 2 subcategories, anxiety and depression, with a total of 14 questions, consisting of 7 questions for anxiety and 7 questions for depression. Each question is based on a 3-point scale, with a total of 21 points possible for each subcategory of anxiety and depression. A higher score indicates a high degree of anxiety and depression, where 0 to 7 points indicate no anxiety and depression, 8 to 10 points suspect anxiety and depression, and >11 points indicate anxiety and depression.^[21]^ Moreover, the total scores refer to a combination of anxiety and depression scores and classified as mild, ranging from 8 to 10, moderate from 11 to 14, and severe from 15 to 21 points.^[22]^ Measurements are taken at the baseline, 2 weeks, 4 weeks, 6 weeks, and 10 weeks after treatment.

##### Montreal Cognitive Assessment Korean version (MoCA-K)

2.5.2.4

The Korean version of Montreal Cognitive Assessment is a tool developed to examine mild cognitive impairment.^[23]^ It consists of 30 points in total, consisting of short-term memory test (5 points), clock drawing for space-time function (3 points) and 3-dimensional block drawing tests (1 point), trail-making test B for performance (1 point), language fluency test (1 point) and 2-item verbal abstraction task (2 points), concentration maintenance test to test concentration (1 point), subtraction in order (3 points), digit span forward and backward (2 points), animal names (3 points) and following speaking complex phrases (2 points), and disorientation for time and place (6 points). If the total score is <22, mild cognitive impairment can be suspected. Moreover, mild cognitive impairment score ranges from 18 to 26 points, moderate from 10 to 17 points, and severe if <10 points. Measurements are taken at the baseline, 2 weeks, 4 weeks, 6 weeks, and 10 weeks after treatment.

